# List of used acronyms and abbreviations

| **Abbreviation** | **Term/Explanation** |
| --- | --- |
| AE | Adverse Event = any untoward medical occurrence |
| AR | Adverse Reaction = adverse event, that is each unfavorable and unexpected reaction to a study treatment, regardless of dose |
| CRF | Case Report Form |
| DSUR | Development Safety Update Report = annual safety report |
| GCP | Good Clinical Practice |
| ICH | International Council for Harmonization |
| IMP | Investigational medicinal product |
| ITT | Intention-to-treat = including all data from all subjects who have participated in the study |
| LVFS | Läkemedelsverkets författningssamling (in English: Swedish Medical Products Agency’s statutes) |
| PP | Per Protocol analysis = including only data from subjects who have completed the study completely in accordance with the protocol, with no deviations from the protocol |
| SAE | Serious Adverse Event = serious untoward medical occurrence. SAEs include all serious events independent of whether they have a suspected causal relationship to the IMP or not. |
| SmPC | Summary of Product Characteristics |
| SUSAR | Suspected Unexpected Serious Adverse Reaction |
|  |  |
|  |  |

#

1. Synopsis

| EudraCT number: 2021-000349-42 |
| --- |
| Title: Evaluation of the Durability of Immune Responses to SARS-CoV-2 Using Novel Rapid Spike Interferon-Gamma Release and Activation-Induced Marker Assays and Anti-Spike IgG Following COVID-19 Vaccination |
| Study code: DurIRVac |
| Short background/Rationale/Aim: Vaccination against COVID-19 has now commenced in Sweden, although the durability of immune responses following vaccination for COVID-19 remains unclear. |
| Primary objective: To evaluate the durability of immune responses following vaccination for COVID-19 among immunocompromised, cirrhotic, renal insufficient and healthy participants using novel rapid spike interferon-γ release and activation-induced marker assays and anti-spike IgG serology, aiming at identifying correlates of vaccine-induced protection. |
| Study design: Phase IV post marketing surveillance, observational prospective cohort study |
| Study population: Immunocompromised, cirrhotic, renal insufficient and healthy participants |
| Number of subjects: 500 |
| Inclusion criteria:  1. Participants must give written informed consent  2. Woman or man aged 18 years or older undergoing vaccination against COVID-19 in Region Västra Götaland in accordance with clinic routine and regional prioritization. |
| Exclusion criteria:  1. Inability to give written informed consent  2. Inability to undergo blood sampling, for example lack of suitable blood vessels for sampling |
| Investigational product(s): The COVID-19 vaccines currently approved by EMA and in use in Region Västra Götaland:   1. Comirnaty, EMEA/H/C/005735, BioNTech Manufacturing GmbH 2. COVID-19 Vaccine Moderna, EMEA/H/C/005791, Moderna Biotech Spain, S.L. 3. COVID-19 Vaccine AstraZeneca, EMEA/H/C/005675, AstraZeneca AB. |
| Primary endpoint:  Levels achieved immediately before the 1^st^ and 2^nd^ doses, 4 weeks post-2^nd^ dose, and then every 3 months for 2 years for the following analyses:   1. anti-RBD Spike IgG quantitative serology calibrated against a WHO standard (Abbott) 2. a novel rapid spike interferon-γ release assay 3. a novel rapid spike activation-induced marker assay |
| Study period:  Q1 2021 – Q3 2023 |
| End of trial:  Q4 2023 |

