# Background and rationale

Vaccination against COVID-19 has now commenced in Sweden, although the durability of immune responses following vaccination for COVID-19 remains unclear. The primary aim is to evaluate the durability of immune responses following vaccination for COVID-19 among immunocompromised, cirrhotic, renal insufficient and healthy participants using novel rapid spike interferon-γ release and activation-induced marker assays and anti-spike IgG serology, aiming at identifying correlates of vaccine-induced protection. Secondary aims include evaluating the impact of prior natural exposure to SARS-CoV-2 and human genetic variants on these vaccine responses, monitoring for emergence of vaccine-escape SARS-CoV-2 variants, and creating a large easily accessible biobank for research. To complement the data available through the Swedish National Vaccination Register, participants will enter detailed health-related information pertinent to the study in the case report form (CRF). The study will strive to sample participants immediately before the 1^st^ and 2^nd^ doses, 4 weeks post-2^nd^ dose, and then every 3 months for at least 2 years. Enrollment of participants at timepoints after initiation of vaccination will also be permitted, as sampling prior to vaccination may prove challenging.

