# Primary study objective

The primary objective of this study is to evaluate the durability of immune responses following vaccination for COVID-19.

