3. Anti-spike SARS-CoV-2 IgG serology using the Abbott Architect newly developed assay for the detection of IgG antibodies (SARS-CoV-2 IgG II Quant). The assay is a fully automated CMIA Assay (Chemiluminescent Microparticle Immunoassay) for the qualitative and quantitative (AU/mL) determination of IgG antibodies against SARS-CoV-2, including the spike receptor-binding domain (RBD). This assay will be performed in the Department of Microbiology/Virology at Sahlgrenska University Hospital under the supervision of PI [name].
4. Directed single nucleotide polymorphism (SNP) genetic profiling of participants regarding *Interferon lambda-4* (*IFNL4*), *Inosine triphosphate pyrophosphatase* (*ITPA*), *NOX2*, *HLA-genotype, CD46, Interleukin 1,2,6,10 and12,* Blood group, *TLR3, UNC93B1, TICAM1, TBK1, IRF3, IRF7, IFNAR1, IFNAR2, RF7, IFNAR1*. These assays will be performed in the laboratory of PI [name].
5. Continuous monitoring for virological evidence of breakthrough post-vaccination SARS-CoV-2 infection via data obtained from the laboratory information system (LIS) at the Department of Clinical Microbiology/Virology, Gothenburg. These vaccine-breakthrough viruses will be sequenced (in particular regarding the spike protein) for evidence of vaccine escape mutants. Possible viral breakthrough variants will also be cultured in the BSL-3 laboratory and evaluated regarding sensitivity to neutralizing antibodies following vaccination and natural exposure.

The following analyses will be performed on samples from selected participants (e.g. those belonging to risk groups or other relevant subsets having received the various vaccines administered):

1. More extensive T-cell analyses evaluating possible immunologic memory after vaccination in the laboratory of Associate [name].
2. Neutralizing antibody titration will be performed in the Biosafety Level 3 (BSL-3) laboratory at the Department of Microbiology/Virology at Sahlgrenska University Hospital. These analyses will be performed under the supervision of Associate [name].
3. Genome-wide single nucleotide polymorphism sequencing for genome-wide association study (GWAS) using Illumina Infinium SNP Genotyping Arrays at National Genomics Infrastructure (NGI Sweden), SciLifeLab

##

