# Methods for measurement of endpoints for clinical efficacy and safety

- 1. Methods for measurement of endpoints for clinical efficacy

Levels achieved using the methods below will be monitored immediately before the 1^st^ and 2^nd^ vaccine doses, 4 weeks post-2^nd^ vaccine dose, and then every 3 months for 2 years for the following analyses:

1. anti-RBD Spike IgG quantitative serology calibrated against a WHO standard (Abbott)
2. a novel rapid spike interferon-γ release assay
3. a novel rapid spike activation-induced marker assay
   1. Primary endpoint (variable)

The primary endpoints (variables) are the levels achieved using the abovementioned assays, which will be monitored immediately before the 1^st^ and 2^nd^ vaccine doses, 4 weeks post-2^nd^ vaccine dose, and then every 3 months for 2 years. This study is an open phase IV post marketing surveillance, observational prospective cohort study.

- 1. Methods for measurement of endpoints (variables) for clinical safety

The endpoint(s) (variables) for clinical safety will be the reported adverse events (AE) and serious adverse events (SAE). This analysis will be performed continuously during the study.

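### The Synopsis and Background make correlates of protection part of the primary aim, but no infection outcome is defined and the only stated source of infections is one laboratory's system

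*Protocol*

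**What the plan says.** **Aim.** The Synopsis (Primary objective) describes a study of durability in immunocompromised, cirrhotic, renally impaired and healthy participants, "aiming at identifying correlates of vaccine-induced protection". Background and rationale repeats this within the primary aim: "anti-spike IgG serology, aiming at identifying correlates of vaccine-induced protection". The Primary study objective section stops earlier: "The primary objective of this study is to evaluate the durability of immune responses following vaccination for COVID-19".

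**Endpoints.** Methods for measurement of endpoints states: "The primary endpoints (variables) are the levels achieved using the abovementioned assays". The three assays are a spike interferon-γ release assay, a spike activation-induced marker assay and anti-RBD spike IgG. The Synopsis and the Primary endpoint (variable) section list the same three. The only other endpoints are for safety: "The endpoint(s) (variables) for clinical safety will be the reported adverse events (AE) and serious adverse events (SAE". The secondary aims in the Background cover prior natural exposure and human genetic variants, followed by "monitoring for emergence of vaccine-escape SARS-CoV-2 variants, and creating a large easily accessible biobank for research".

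**Infection data.** Item 5 of the analyses planned for all participants, under Overall study design, reads: "Continuous monitoring for virological evidence of breakthrough post-vaccination SARS-CoV-2 infection via data obtained from the laboratory information system (LIS". The system belongs to the Department of Clinical Microbiology/Virology in Gothenburg. The stated use of the viruses found is sequencing for escape mutants, with culture and neutralisation-sensitivity testing of possible variants.

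**The concern.** A correlate of protection is a relation between an immune level and the later occurrence of infection. The protocol specifies the level in detail but does not define the infection side: it gives no endpoint, no case definition and no statement that infections will be set against the assay results.

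Ascertainment matters more than wording here. How a correlate is modelled can be settled later in a statistical analysis plan. A positive test that nobody recorded during two years of follow-up cannot be recovered there. If the laboratory system is the only source, a participant who tested positive through another laboratory would enter any such analysis as uninfected. What is at stake is whether the correlates part of the stated primary aim can be answered from the data the study collects.

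**Working it through.** **Step 1. Sections side by side.**

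| Section | Content | Infection as an outcome |
|---|---|---|
| Synopsis, Primary objective | Durability plus correlates | Needed, not defined |
| Background and rationale | Same primary aim; secondary aims listed | Needed, not among the secondary aims |
| Primary study objective | Durability only | Not needed |
| Synopsis, Primary endpoint; Primary endpoint (variable); Methods for measurement of endpoints | Levels in three assays | Absent |
| Methods for measurement, clinical safety | AE and SAE | Not named |
| Overall study design, item 5 | Laboratory-system monitoring, sequencing, culture | Monitored, not an endpoint |

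Two results follow. The Synopsis and Background disagree with the Primary study objective section on whether correlates belong to the primary objective. Where correlates are claimed, no outcome supports the claim.

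**Step 2. Catchment against ascertainment.** The inclusion criteria admit adults vaccinated in Region Västra Götaland. Screening narrows recruitment to patients attending Sahlgrenska University Hospital clinics and staff of two of its departments. Infections are sought in one Gothenburg department's system. The protocol does not say that all positive tests in these participants reach that system. The Background says participants will enter health information in the CRF, without naming infections or test results.

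**Step 3. The plan's own figure.** Statistics gives five groups of about 100: 5 × 100 = 500, which agrees with the Synopsis. The figure is a sum only. The section says a statistical basis is hard to provide and gives no infection rate, effect size, alpha or power.

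**Step 4. Can the size of the loss be derived?** It cannot, because neither the infection rate nor the captured share is in the document. An illustration shows how far the answer moves. All inputs except 500 are assumptions: cumulative infection p of 2-20%, captured share c of 100% or 40%, two-sided alpha 0.05, participants split equally into high and low level, hazard ratio 0.5.

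- Recorded infections: D = 500 × p × c.
- Infections needed for 80% power (Schoenfeld): (1.960 + 0.842)² / (0.25 × (ln 0.5)²) = 7.849 / 0.1201 = 65.3, so 66.
- Power: Φ(½ × √D × 0.693 − 1.960). For D = 25 this is Φ(1.733 − 1.960) = 41%.

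| p | D at c = 100% | Power | D at c = 40% | Power |
|---|---|---|---|---|
| 2% | 10 | 19% | 4 | 10% |
| 5% | 25 | 41% | 10 | 19% |
| 10% | 50 | 69% | 20 | 34% |
| 20% | 100 | 93% | 40 | 59% |

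The table counts only the loss of events and makes no allowance for bias. It shows that the share captured matters at every assumed rate. It does not show which row or column applies.

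**The case against.** The strongest reply is that this is a durability study. The title, the Primary study objective section and all the primary endpoints agree on that, and the correlates wording is a trailing clause. That is fair, and it is why deleting the clause is an acceptable remedy. But the clause stands inside the stated primary objective in the Synopsis and the primary aim in the Background, so one text or the other has to change.

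A second reply is that capture may be good. Recruitment from Sahlgrenska clinics and staff is narrower than the regional eligibility and plausibly closer to the Gothenburg system. The CRF may already ask about infections, and the secondary aim on prior exposure would need such a history. This stands as a limit: poor capture is not shown. The protocol does not, however, state that capture is secured.

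A third reply is that correlate modelling belongs in an analysis plan. That is right for the choice of model and for which earlier level is used. It does not cover the outcome or how it is found.

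A reader might also infer three stronger points, which the protocol does not support:

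- **That neutralisation is confined to hand-picked risk groups and this undermines the aim.** The text says "selected participants (e.g. those belonging to risk groups or other relevant subsets having received the various vaccines administered", so risk groups are an example. The aim is tied to three other assays, which are run on all participants, and stored samples leave later testing open.
- **That missed infections would create a false correlate.** The protocol describes no correlate analysis. The direction depends on which levels are used: with pre-infection levels, missed infections unrelated to level would tend to dilute an association.
- **That there will be too few events.** This rests wholly on assumed rates, and the illustration runs from inadequate to ample power.

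**Conclusion.** The point holds in this form: the primary aim as given in the Synopsis and Background includes correlates of protection, the Primary study objective section does not, no infection outcome is defined, and the only stated source of infections is one department's laboratory system. Positive tests processed elsewhere would be missed unless the undescribed CRF records them.

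The inconsistency and the missing outcome rest on the text alone. The number of infections lost cannot be derived from the document, and the power range of about 10% to 93% is an illustration on assumed inputs, not an estimate. The durability endpoints are untouched, so this should be corrected but does not threaten the study's main analysis.

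**What to change.** **Option A, keep the aim.** Name first documented SARS-CoV-2 infection after dose 2 as a secondary endpoint. Ascertain it from the laboratory system plus a CRF question at each scheduled visit on any positive test anywhere, with its date. State that infections will be related to levels measured before infection; the date makes that possible, and the detailed rule can sit in the analysis plan. Bring the Primary study objective section into line with the Synopsis and Background.

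The cost is small because the visits exist already. Sampling every 3 months for 2 years gives 24 / 3 = 8 visits, and the visit 4 weeks after dose 2 makes 9. That is at most 9 × 500 = 4,500 short answers with full attendance. The downside is that some self-reported tests will need checking.

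**Option B, drop the aim.** Delete the correlates wording from the Synopsis and the Background so that both agree with the Primary study objective section. This costs nothing in data collection but gives up the claim.

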# Background and rationale

Vaccination against COVID-19 has now commenced in Sweden, although the durability of immune responses following vaccination for COVID-19 remains unclear. The primary aim is to evaluate the durability of immune responses following vaccination for COVID-19 among immunocompromised, cirrhotic, renal insufficient and healthy participants using novel rapid spike interferon-γ release and activation-induced marker assays and anti-spike IgG serology, aiming at identifying correlates of vaccine-induced protection. Secondary aims include evaluating the impact of prior natural exposure to SARS-CoV-2 and human genetic variants on these vaccine responses, monitoring for emergence of vaccine-escape SARS-CoV-2 variants, and creating a large easily accessible biobank for research. To complement the data available through the Swedish National Vaccination Register, participants will enter detailed health-related information pertinent to the study in the case report form (CRF). The study will strive to sample participants immediately before the 1^st^ and 2^nd^ doses, 4 weeks post-2^nd^ dose, and then every 3 months for at least 2 years. Enrollment of participants at timepoints after initiation of vaccination will also be permitted, as sampling prior to vaccination may prove challenging.

# Benefit-risk evaluation

**Benefit:** By participating in the study, the participants can relatively rapidly find out if they have antibodies to SARS-CoV-2 via Direkttest.se if the sampling was registered there, which is the current clinical routine. The participants also contribute to development and furthering of knowledge with regards to COVID-19.

**Risk:** The participant will provide an extra serum tube (9 mL), three lithium-heparin tubes without gel (24 mL) and a saliva sample at each sampling other than that included in routine clinical practice. The discomfort of sampling and the invasion of integrity is considered minor. All statistical processing, compilation and reporting of the material takes place with the help of a decoded database in which the participants' identities remain unknown.

The scientific value of the study is judged to be great. The discomfort of sampling and the invasion of integrity is considered minor. Participants can relatively easily decide for themselves and thus make an informed decision about possible participation.

# Primary study objective

The primary objective of this study is to evaluate the durability of immune responses following vaccination for COVID-19.

## Primary endpoint (variable)

Primary variable: Levels achieved immediately before the 1^st^ and 2^nd^ doses, 4 weeks post-2^nd^ dose, and then every 3 months for at least 2 years for the following analyses:

1. a novel rapid spike interferon-γ release assay
2. a novel rapid spike activation-induced marker assay
3. anti-RBD Spike IgG serology (Abbott)

# Study design and procedures

## Overall study design

This study is an open phase IV post marketing surveillance, observational prospective cohort study. The researchers involved in this study have no influence or input with regards to which COVID-19 vaccine the participants receive, the number of vaccine doses, nor the timepoint of vaccination. The vaccination will be performed by healthcare providers in Region Västra Götaland in accordance with national and regional prioritization as well as the clinic routine.

Investigational products are the COVID-19 vaccines currently approved by EMA and in use in Region Västra Götaland, i.e.:

1. Comirnaty, EMEA/H/C/005735, BioNTech Manufacturing GmbH
2. COVID-19 Vaccine Moderna, EMEA/H/C/005791, Moderna Biotech Spain, S.L.
3. COVID-19 Vaccine AstraZeneca, EMEA/H/C/005675, AstraZeneca AB.

Region Västra Götaland, unlike any other region in Sweden, has negotiated access via Data&Analys to data from the Swedish National Vaccination Register for Covid-19 at an individual vaccinee level rather than on a population-based level. This data consists of (1) Date of vaccination, (2) Which vaccine was used, (3) Lot number, (4) Dose number, and (5) Healthcare provider that performed the vaccination. Currently it remains unclear whether information regarding possible redosing of vaccine will be available from the National Vaccination Register.

After obtaining informed consent, participants will be sampled (1 serum tube (9 mL), 3 litium-heparin tubes without gel (24 mL) and saliva) immediately before the 1^st^ and 2^nd^ doses (if this is not possible logistically, these samples may be obtained during the recommended 15-30 minute observation period after COVID vaccination), 4 weeks post-2^nd^ dose, and then every 3 months for a total of 2 years. Enrollment of participants at timepoints after initiation of vaccination will also be permitted, as sampling prior to vaccination may prove challenging. Sampling will be registered using Direkttest.se as currently is the norm.

The following analyses will be performed on samples from all participants:

1. a novel rapid spike interferon-γ release assay will be performed in the laboratory of Associate [name].
2. a novel rapid spike activation-induced marker assay will be performed in the laboratory of Associate [name].
3. Anti-spike SARS-CoV-2 IgG serology using the Abbott Architect newly developed assay for the detection of IgG antibodies (SARS-CoV-2 IgG II Quant). The assay is a fully automated CMIA Assay (Chemiluminescent Microparticle Immunoassay) for the qualitative and quantitative (AU/mL) determination of IgG antibodies against SARS-CoV-2, including the spike receptor-binding domain (RBD). This assay will be performed in the Department of Microbiology/Virology at Sahlgrenska University Hospital under the supervision of PI [name].
4. Directed single nucleotide polymorphism (SNP) genetic profiling of participants regarding *Interferon lambda-4* (*IFNL4*), *Inosine triphosphate pyrophosphatase* (*ITPA*), *NOX2*, *HLA-genotype, CD46, Interleukin 1,2,6,10 and12,* Blood group, *TLR3, UNC93B1, TICAM1, TBK1, IRF3, IRF7, IFNAR1, IFNAR2, RF7, IFNAR1*. These assays will be performed in the laboratory of PI [name].
5. Continuous monitoring for virological evidence of breakthrough post-vaccination SARS-CoV-2 infection via data obtained from the laboratory information system (LIS) at the Department of Clinical Microbiology/Virology, Gothenburg. These vaccine-breakthrough viruses will be sequenced (in particular regarding the spike protein) for evidence of vaccine escape mutants. Possible viral breakthrough variants will also be cultured in the BSL-3 laboratory and evaluated regarding sensitivity to neutralizing antibodies following vaccination and natural exposure.

The following analyses will be performed on samples from selected participants (e.g. those belonging to risk groups or other relevant subsets having received the various vaccines administered):

1. More extensive T-cell analyses evaluating possible immunologic memory after vaccination in the laboratory of Associate [name].
2. Neutralizing antibody titration will be performed in the Biosafety Level 3 (BSL-3) laboratory at the Department of Microbiology/Virology at Sahlgrenska University Hospital. These analyses will be performed under the supervision of Associate [name].
3. Genome-wide single nucleotide polymorphism sequencing for genome-wide association study (GWAS) using Illumina Infinium SNP Genotyping Arrays at National Genomics Infrastructure (NGI Sweden), SciLifeLab

##

